## Methods

### Design and Study Population

This study was designed in accordance with the COSMIN (Consensus-Based Standards for the Selection of Health Measurement Instruments) Study Design checklist for patient-reported outcome measurement [24] and the COSMIN methodology for evaluating the content validity of patient-reported outcome measures [25]. The qualitative descriptive investigation in this study adheres to the guidelines outlined in the COREQ (Consolidated Criteria for Reporting on Qualitative Research) checklist [26].

The criteria for identifying patients with HF in this study are defined as follows. The eligible population includes patients aged ≥18 years with symptomatic HF (stage C), according to the American College of Cardiology/American Heart Association/Heart Failure Society of America guidelines [1]. Under the Japanese long-term care insurance system, individuals aged ≥65 years are assessed and classified into 7 levels of care needs based on their activities of daily living, cognitive function, and medical conditions. For patients aged ≥65 years, only those yet to receive long-term care certification or those who fall within the range of “Requiring Help 1” to “Long-term Care Level 1” will be included. This is because the SEBS-HF is aimed at home-based patients with HF who can self-manage their diet to some extent, focusing on individuals who are relatively independent but may still require minimal assistance.

The exclusion criteria are as follows: living in care facilities, assisted living facilities, or nursing homes; aged ≤65 years with a disability certificate unrelated to cardiac dysfunction; undergoing hemodialysis because of dietary restrictions different from those of patients with HF; chronic respiratory diseases because of symptoms similar to HF such as reduced exercise tolerance; and mental illnesses because of the potential impact on eating behaviors.

Patients with HF eligible for this study will be recruited from either outpatients or inpatients at the medical institutions where the coresearchers are affiliated and the medical institutions collaborating in this study. Specifically, patients who are attending or admitted to the cardiology departments of these medical institutions will be included.

Experts will be recruited through the network of the principal investigator and coresearchers, and snowball sampling of the initially recommended experts.

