### Preliminary Investigation

Data will be collected using clinical records, self-administered questionnaires, and the preliminary SEBS-HF. To confirm normality, the sample size will be approximately 30 [30]. In addition, data will be collected from patients attending collaborating medical institutions. The principal investigators collaborating at these institutions will select patients based on established eligibility criteria. Once informed consent has been obtained, the patient’s clinical records will also be collected. A survey set, which includes the self-administered questionnaire and preliminary SEBS-HF, will be provided along with a return envelope for data collection. Calculations will be made from the acquired data to determine the mean scores, standard deviations, and individual item score distributions. Normality tests will be also performed. Moreover, potential ceiling and floor effects will be examined based on the mean and standard deviation.

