### Primary Investigation

The reliability and validity of the data acquired from the primary investigation will be examined using statistical methods (Table 1).

**Table 1 table1:** Statistical analysis procedures and considerations for assessing reliability and validity.

Statistical analysis	Procedure
Descriptive statistics	Measure means, SDs, and frequencies
Normality assessment	Conduct a Shapiro-Wilk test, which calculates a test statistic based on the observed data and compares it against the Shapiro-Wilk distribution.
Item analysis	Evaluate ceiling and floor effects and perform item-total correlation analysis. Items with a correlation coefficient *r* <0.3 or >0.7 may be considered for removal or integration [31].
Internal consistency	Calculate Cronbach α coefficient. A coefficient of ≥0.7 is considered to indicate internal consistency [32].
Structural validity	Perform an exploratory factor analysis to ascertain the degree of shared variance among the items and elucidate potential factor groupings. The factor structure established through exploratory factor analysis is assessed with confirmatory factor analysis to check its fit with data from a different population.
Criterion validity	Calculate descriptive statistics for the external criterion scale and confirm normality. Then, calculate the correlation coefficient between the criterion scale and the scale under development. The validity is evaluated based on the value of the correlation coefficient.
Construct validity	Calculate the correlation coefficient between subgroups to verify hypotheses. In this scale, it is assumed that aging and the decline in physical and mental functions due to HF^a^ symptoms will affect eating behavior negatively. Therefore, verification will be done using age, NYHA^b^ classification [1], and certification of care-need level subgroups.
Measurement error	Calculate the intraclass correlation coefficient, SE, and detectable minimum change for the total scale and subscale scores obtained from the first and second tests. The sample size should be >50 participants to verify measurement error. An intraclass correlation coefficient of ≥0.7 is considered to indicate stability [33].

^a^HF: heart failure.

^b^NYHA: New York Heart Association.

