In addition to the data collection methods used in the preliminary investigation, the primary investigation will incorporate the test-retest method to assess measurement error and establish scales to evaluate criterion-related validity. In the test-retest method, participants will initially respond to the SEBS-HF and then provide their responses again 2 weeks later. To assess the criterion-related validity of the SEBS-HF, we will select the Medical Outcomes Study 36-Item Short-Form Health Survey [34] and the EHFScBS [8] as external measures. We will request the study participants to provide their responses to these instruments. If more suitable external measures are available when the survey commences, we may opt to use them.

The maximum likelihood method and promax rotation will be used in the exploratory factor analysis. The factor loadings obtained will enable commonality assessment among the questionnaire items. Items with a factor loading exceeding a certain threshold will be selected. Consideration will be given to the excluded items that did not meet this threshold or loaded on multiple factors. If items are excluded, a factor analysis will be performed again.

The factor structure established by exploratory factor analysis will be examined to fit the data collected from different populations. This will be performed using goodness of fit indices (goodness-of-fit index, adjusted goodness-of-fit index, comparative fit index, and root mean square error of approximation) to evaluate the appropriateness of the model. If the fit does not meet specific standards, a review of the questionnaire items or reconsideration of the exploratory factor analysis will be needed.

According to the COSMIN guidelines [24], the sample size should be 5-7 times the number of scale items and not <100. Assuming the scale had 30 items, we planned to include more than 150 participants in the primary investigation. Data from different populations are required to conduct exploratory and confirmatory factor analyses. Therefore, the total sample size should exceed 300 participants.

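### The 2-week retest is not restricted to stable patients living at home, although inpatients are eligible, so real change can be counted as measurement error

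*Protocol article*

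**What the plan says.** Under Design and Study Population, one frame serves all phases: "Patients with HF eligible for this study will be recruited from either outpatients or inpatients at the medical institutions", made specific as "patients who are attending or admitted to the cardiology departments of these medical institutions will be included". The same section says that "the SEBS-HF is aimed at home-based patients with HF who can self-manage their diet to some extent".

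Under Preliminary Investigation, the survey text is narrower in one phrase and general in the next: "data will be collected from patients attending collaborating medical institutions", while the institutions' investigators "select patients based on established eligibility criteria". Under Primary Investigation, these methods carry over: "In addition to the data collection methods used in the preliminary investigation, the primary investigation will incorporate the test-retest method to assess measurement error". The retest rule is that "participants will initially respond to the SEBS-HF and then provide their responses again 2 weeks later".

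Table 1 (Measurement error) takes the ICC, the standard error and the minimum detectable change, for total and subscale scores, from the two responses in more than 50 participants. It adds: "An intraclass correlation coefficient of ≥0.7 is considered to indicate stability".

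**The concern.** ICC, SEM and MDC describe measurement error only if a patient's true score is the same at both responses. The stated design does not secure this. A patient who first answers while admitted may be at home two weeks later, and for a scale about managing one's diet at home that is a change of circumstances. The plan also expects clinical change to move the score: the construct-validity row of Table 1 assumes that functional decline from heart-failure symptoms affects eating behaviour. The same problem applies, with less force, to outpatients whose condition changes within the interval.

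Two results are at stake. A scale that is reliable in stable patients would look less reliable against the plan's own criterion. The published MDC would also be too large, so later users would dismiss real changes as noise.

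**Working it through.** **What the text permits.** Eligibility includes admitted patients. The survey description speaks of attending patients, a word that Design and Study Population sets against admitted ones, but it selects by the general eligibility criteria. The retest sentence adds no limit. Inpatients are therefore permitted in the retest, but nothing says that they will be in it.

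**The plan's own figures.** 5 × 30 items = 150 and 2 × 150 = 300, as stated. The retest minimum (more than 50) and the 0.7 criterion are given without derivation, so there is no retest figure to reproduce.

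**Inputs.** From the article: a 2-week interval, more than 50 retesters, and ICC, SE and MDC as the measures. Assumed, because the article gives none of them: observed score variance 1 (so changes are in SD units); true ICC 0.80, hence true-score variance 0.80 and error variance 0.20; a share p of retesters whose true score changes with mean m and SD s, independently of the first score; no change in the rest.

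**Formulas.**
- Variance of change over all retesters: V_D = p(s² + m²) − (pm)²
- Residual variance: V_res = 0.20 + V_D/2
- Variance between occasions: V_time = (pm)²/2
- ICC, consistency = 0.80/(0.80 + V_res)
- ICC, agreement = 0.80/(0.80 + V_res + V_time)
- MDC = 1.96 × √2 × SEM, so the MDC ratio is √(V_res/0.20) with the mean shift removed, or √[(V_res + V_time)/0.20] with it included

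**One case in full** (p = 0.30, m = 0.5, s = 0.8): V_D = 0.30 × 0.89 − 0.15² = 0.2445. V_res = 0.20 + 0.12225 = 0.32225. V_time = 0.01125. ICC agreement = 0.80/1.1335 = 0.706. ICC consistency = 0.80/1.12225 = 0.713. MDC ratio = √1.611 = 1.27, or 1.29 with the mean shift included.

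| p | m | s | ICC agreement | ICC consistency | MDC rise, shift removed | MDC rise, shift included |
|---|---|---|---|---|---|---|
| 0 | – | – | 0.800 | 0.800 | 0 | 0 |
| 0.20 | 0.3 | 0.5 | 0.774 | 0.775 | 8% | 8% |
| 0.30 | 0.3 | 0.5 | 0.761 | 0.764 | 11% | 12% |
| 0.20 | 0.5 | 0.5 | 0.762 | 0.766 | 11% | 12% |
| 0.30 | 0.5 | 0.5 | 0.744 | 0.752 | 15% | 17% |
| 0.20 | 0.5 | 0.8 | 0.735 | 0.738 | 19% | 20% |
| 0.30 | 0.5 | 0.8 | 0.706 | 0.713 | 27% | 29% |

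In simulated samples of 51, the mean agreement ICC in the last row is 0.70, slightly below the large-sample value.

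**Where the effect vanishes.** With p = 0 there is none. If every retester shifts by the same 0.5 SD, the consistency ICC stays at 0.80 and only the agreement form falls, to 0.80/(0.80 + 0.20 + 0.125) = 0.71.

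**The case against.** A reader might infer that the retest will be run in inpatients and that its estimates are therefore biased. The article supports neither step. Its inpatient wording covers every phase, interviews included. The survey text speaks of attending patients and uses take-home forms with a return envelope. The items do not exist yet and no recall period is given, so it is also unknown whether a hospital stay would shift answers about circumstances at home. This stands: the bias is conditional.

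A reader might also put the harm as a reliable scale probably failing the criterion. With true ICC 0.80 and n = 51, the chance of an agreement ICC of at least 0.7 is 95% with no change and 69-54% in the two harshest rows. Those rows depend on the assumed SD of change of 0.8. With 0.5 and the same mean shift the chance is 83-74%, and if 151 patients retest it is about 94-87%. In most of these cases the scale passes, so failure is not the main message.

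The 0.7 rule itself is a cited convention. How the ICC is reported around it is commonly left to the analysis plan, and it is no part of this point.

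Finally, the full protocol may contain a stability check that the article omits. That is possible. But the article does state the interval, the minimum number, the measures and the criterion, and the retest sample that it describes is unrestricted.

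**Conclusion.** The point holds in conditional form. As written, the retest admits patients whose circumstances or condition change within two weeks, and nothing separates that change from measurement error. In the model used here the direction is clear: a mixture of changed and unchanged patients lowers both forms of the ICC and raises SEM and MDC. The size cannot be fixed from the article. Over the assumed range the ICC falls from 0.80 to roughly 0.78-0.70 and the MDC rises by about 8-27% (up to 29% if the mean shift is counted as error). These figures rest on an assumed true ICC, share changed, shift and spread, and on change being independent of the first score.

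This is worth settling before Phase 3 starts, because a patient's stability cannot be recovered reliably once the forms are back.

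**What to change.** 1. Reconcile the eligibility wording under Design and Study Population (attending or admitted) with Preliminary Investigation (attending), and state which applies to the retest.
2. Add one question to the retest form: whether the patient's heart-failure condition or eating circumstances have changed since the first response. Record where the patient was living at each response.
3. Compute the primary ICC, SEM and MDC in patients who were living at home at both responses and report no change. Apply the plan's minimum of more than 50 to this group.
4. Show the remaining retesters separately.

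The cost is one question and somewhat more retest forms. To keep 51 unchanged patients when 20-30% have changed, 51/0.8 = 64 to 51/0.7 = 73 returned retests are needed. They can be drawn from the more than 300 participants already planned, so recruitment need not grow.

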## Introduction

Heart failure (HF) is a clinical syndrome characterized by signs and symptoms resulting from a structural or functional impairment in ventricular filling or blood ejection [1]. HF is a global pandemic, with its prevalence steadily increasing globally, coupled with a consistent increase in associated mortality rates [2]. The prevalence of HF in Japan is estimated to be between 2.2% and 6.5% [3], with HF-related deaths accounting for 6.3% of all mortalities [4]. Given the context of a super-aged society, Japan is currently facing an HF pandemic [5].

Effective self-care for patients with HF primarily involves medication adherence, dietary habits, and physical activity [1]. Self-care measures, such as the European Heart Failure Self-care Behavior Scale (EHFScBS) [6] and the Self-Care of Heart Failure Index (SCHFI) [7], are widely recognized. A Japanese version of the EHFScBS has been developed and used [8]. Patients who adhered to appropriate self-care, as indicated by their EHFScBS scores, had significantly fewer hospitalizations due to all causes than those who did not [9]. The EHFScBS and SCHFI, which include dietary habits as part of self-care, primarily evaluate patient adherence.

Dietary recommendations for preventing HF progression and its associated adverse events are based on balancing sodium restriction with adequate nutrient intake [1]. Concerning low-sodium diets, large-scale randomized controlled trials have demonstrated that stringent sodium restrictions have limited benefits [10]. Therefore, a moderately low-sodium diet and adequate nutritional intake are recommended. However, a low-sodium diet often leads to inadequate intake of macronutrients and micronutrients [11,12]. HF comorbidities, including malnutrition, are known to affect prognosis adversely [13]. In addition, maintaining a balanced diet after discharge from the hospital is crucial to prevent HF progression. Home dietary management entails selecting suitable ingredients and meals, purchasing and preparing them, and making associated decisions. The term “eating behavior” broadly encapsulates these series of actions and decision-making processes [14].

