The Brief Dietary Psychosocial Scale (BDPS) is an instrument that targets adolescents and adults, focusing on psychosocial factors and external environments that influence healthy dietary habits, such as the consumption of fruits, vegetables, fiber/whole grains, and fats [15]. The BDPS assesses whether individuals perceive the benefits they derive from a healthy diet, whether they are trying to maintain or change to a healthy diet, whether they are receiving social support for the diet, whether healthy food ingredients are physically and economically accessible, and whether they are enjoying following a healthy diet. The reliability of this scale has previously been evaluated in patients with HF [16].

The Dietary Sodium Restriction Questionnaire (DSRQ) is designed to assess attitudes, subjective norms, and perceived behavioral control related to dietary sodium restriction in patients with HF and hypertension [17]. Of the 3 DSRQ subscales, the subjective norms are predictive factors for adherence to a low-sodium diet [18].

The Burden Scale In Restricted Diets (BIRD) is a specific instrument developed to assess the burden of low-sodium diets in patients with HF [19]. This questionnaire comprises 14 candidate items for the following dietary-related domains: organization, pleasure, leisure, social life, vitality, and self-rated health.

The International Classification of Functioning, Disability, and Health (ICF) is a framework developed by the World Health Organization that categorizes and describes the health and disability status of individuals [20]. Under the ICF framework, eating behavior pertains to activities and participation domains. Patients with HF often experience decreased exercise tolerance [21], depression, and anxiety [22], which fall under the domains of body function and structure, and social isolation [23], included in the environmental factors domain. These conditions among patients with HF may hinder the eating behaviors necessary for proper home dietary management, potentially leading to acute decompensated HF.

Existing measures, such as the BDPS, DSRQ, and BIRD, focus on factors influencing healthy eating and low-sodium diets but lack a perspective on eating behaviors and do not focus on the body functions and structures domain in the ICF, corresponding to decreased exercise tolerance in HF.

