Despite these reasonable hypotheses, measures focusing on the eating behavior determinants among patients with HF are currently lacking. Therefore, this study aims to develop and validate the Self-Administered Eating Behaviors Scale for Heart Failure (SEBS-HF) to assess the dietary habits of patients with HF living at home.

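### Correlations with the SF-36 and EHFScBS can give convergent but not criterion validity, and the mental-function part of the construct hypothesis is tested only indirectly although the SF-36 is already collected

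*Protocol article*

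**What the plan says.** - **Comparators (Primary Investigation, text).** The article states "To assess the criterion-related validity of the SEBS-HF, we will select the Medical Outcomes Study 36-Item Short-Form Health Survey", and it names the EHFScBS as the second external measure. The section then lets the team switch to other measures if better ones exist by the start of the survey, without naming any. Textbox 2 lists both instruments and adds an unnamed entry for established scales serving the same purpose.
- **Decision rule (Table 1, criterion validity row).** The comparator is called an external criterion scale, and "The validity is evaluated based on the value of the correlation coefficient".
- **Rationale for a new scale (Introduction).** The article says that "measures focusing on the eating behavior determinants among patients with HF are currently lacking". Of the EHFScBS and the SCHFI it says "which include dietary habits as part of self-care, primarily evaluate patient adherence". Of the BDPS, DSRQ and BIRD it says that they "lack a perspective on eating behaviors and do not focus on the body functions and structures domain in the ICF".
- **Construct hypothesis (Table 1, construct validity row).** Ageing, and loss of physical and mental function through HF symptoms, are expected to worsen eating behavior. The check uses subgroups by age, NYHA class and care-need level.
- **Care-need level (Design and Study Population).** It is described for people aged 65 and over and combines daily activities, cognition and medical conditions. Patients in that age group are eligible only if uncertified or between Requiring Help 1 and Long-term Care Level 1.

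**The concern.** Criterion validity means agreement with an accepted standard for the same construct. The case for developing the SEBS-HF is that nothing in HF measures this construct, so the label in Table 1 and the rationale in the Introduction pull against each other. If the label stays, the published scale will carry a claim of criterion validity that rests on correlations with general health and with self-care adherence.

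The second part concerns what the study does test. The construct hypothesis names mental as well as physical function, and the Introduction names depression and anxiety among the conditions expected to hinder eating behavior. The variables chosen to test the hypothesis reach mental function only through one component of one composite. Meanwhile the SF-36 is in the survey set but is tied to no hypothesis.

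**Working it through.** **1. Does either comparator qualify as a criterion on the article's own account?**

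| Instrument | What the article says of it | Same construct as the SEBS-HF? |
|---|---|---|
| SF-36 | Named as a health survey; no link to eating behavior is given | No |
| EHFScBS | Covers dietary habits within self-care, but is said to "primarily evaluate patient adherence" | In part; related, not the same |
| BDPS, DSRQ, BIRD (not chosen) | Closest diet instruments, but said to lack an eating-behavior perspective | No, by the article's own description |

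None of the instruments discussed is presented as a standard for eating behavior and its determinants in HF. Replacing the SF-36 or EHFScBS with one of the three diet instruments would give a closer comparator, but still not a criterion.

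**2. What could a correlation show?** A high r with the SF-36 could mean that the new scale tracks eating behavior that depends on health, or that it largely repeats general health status. A high r with the EHFScBS could likewise reflect adherence. A low r with either could mean a poor scale, or a sound scale of something else. Each result has a reading for and against the SEBS-HF. The correlation becomes informative only against a stated expectation, which makes it hypothesis testing and not criterion validity.

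**3. Is sample size the problem?** The article gives no figure for this analysis. Its sample size reproduces: 5 per item x 30 items = 150, and two samples for exploratory and confirmatory factor analysis give 2 x 150 = 300. It does not say which of these enters the correlations, so both are shown. The 95% CI by Fisher z is tanh(atanh(r) ± 1.96/√(n−3)):

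- n = 150: half-width on the z scale 1.96/√147 = 0.162. For r = 0.30, z = 0.310 and the CI is 0.15 to 0.44. For r = 0.70, z = 0.867 and the CI is 0.61 to 0.77.
- n = 300: half-width 1.96/√297 = 0.114. For r = 0.30 the CI is 0.19 to 0.40. For r = 0.70 it is 0.64 to 0.75.

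The values of r are illustrations. The correlations will be estimated with fair precision at either size. The difficulty is what they mean, and more patients would not change that.

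**4. How far do the construct variables cover the hypothesis?**

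| Variable | Mental component in the article |
|---|---|
| Age | None stated |
| NYHA class | None stated |
| Care-need level | Cognition, as one of three elements |

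So one of three has a mental component. It is a composite, it is described only from age 65, and eligibility cuts off its upper range. The article does not say that it reflects depression or anxiety.

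**The case against.** The strongest reply has four parts.

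- **It is only terminology.** The same correlations are computed under either label. That is true of the computation, but not of the conclusion. A criterion claim tells users that the scale agrees with a standard, and here there is none.
- **The EHFScBS is not an arbitrary choice.** It includes dietary habits, so a correlation is meaningful. This stands, and it is why the result counts as convergent evidence. Similarly, the Introduction's remark about lacking measures is a gap statement; it does not say that no external comparator is possible, and this point does not claim so.
- **The comparators are provisional.** The substitution sentence concedes that better ones may appear. It names none, so it does not resolve the mismatch.
- **Expected correlations may be set out elsewhere.** An article can leave cut-offs to a fuller document, so their absence is not a finding. The mismatch between criterion and construct is in the text itself and does not depend on a missing threshold.

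A reader might also infer two stronger things that the article does not support. One is that almost any correlation would pass because small values reach significance in a sample this large, so that the rule could never fail. The criterion row uses no significance test, and the article does not say that all 300 patients enter the correlation. The other is that none of the construct variables touches mental function. The description of care-need levels includes cognition, so that is wrong.

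**Conclusion.** The point holds in this form. Neither of the two named comparators can serve as a criterion for the SEBS-HF on the article's own description. Their correlations support convergent validity at most. The construct hypothesis covers physical and mental function, but mental function is reached through one of three variables, and only as cognition within a restricted composite. Depression and anxiety are not tested directly.

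The conclusion rests on the usual meaning of criterion validity and on the article's wording. The remedy rests on one assumption: the article does not describe SF-36 scoring, so the sponsor should confirm that the Japanese version in use yields separate physical and mental scores. The data to be collected stay usable. What changes is the claim that they can carry.

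**What to change.** 1. Rename the criterion row of Table 1 as convergent (hypothesis-testing) validity, change the matching sentence in the Primary Investigation text and the entry in Textbox 2, and drop the claim of criterion validity.
2. Add the SF-36 physical and mental scores to the construct validity row as a direct test of the stated hypothesis, alongside age, NYHA class and care-need level.
3. Before Phase 3 data collection, fix the comparators and state for each the expected direction and a size that the sponsor justifies. That size should allow for the exclusion of patients with mental illness, which is likely to narrow the spread of mental scores.
4. Report each correlation with its 95% CI, and say which expectations were met.

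The cost is wording and the work of justifying the expected sizes. Both instruments are already in the survey set, so no patients, questionnaires or visits are added. The downside is that the paper can no longer claim criterion validity.

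### At 30 items and about 150 patients, a correct factor model is expected to give GFI near 0.85 and AGFI near 0.82, so neither index should decide whether the structure fits

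*Protocol article*

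**What the plan says.** All of this is in the protocol article, Methods, Primary Investigation, with Table 1.

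- Sample size follows a rule attributed to COSMIN: "the sample size should be 5-7 times the number of scale items and not <100". It is applied as "Assuming the scale had 30 items, we planned to include more than 150 participants in the primary investigation".
- The figure is then doubled: "Data from different populations are required to conduct exploratory and confirmatory factor analyses", and "Therefore, the total sample size should exceed 300 participants".
- Confirmatory fit is judged on "goodness-of-fit index, adjusted goodness-of-fit index, comparative fit index, and root mean square error of approximation".
- The consequence of misfit is stated: "If the fit does not meet specific standards, a review of the questionnaire items or reconsideration of the exploratory factor analysis will be needed".
- The item set can shrink before the confirmatory step. In Table 1, items with extreme item-total correlations "may be considered for removal or integration". After the exploratory analysis, "If items are excluded, a factor analysis will be performed again".

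The article gives no numerical fit standard, no rule for combining the four indices, and no description of which data would test a revised structure.

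**The concern.** GFI and AGFI depend on sample size and on the number of items even when the model is exactly right. Sampling noise in the covariance matrix counts against them, and with many items and few patients there is a lot of it. CFI and RMSEA adjust for the model's degrees of freedom and are much less affected.

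The article sizes the study by a patients-per-item ratio and does not relate that size to the indices chosen to judge fit. If GFI or AGFI carries weight in the decision, the outcome partly reflects sample and model size and not the quality of the scale. Sound items could then be reviewed, or a correct factor structure reopened, for no substantive reason. Structural validity is a central claim of a scale-development study, so this matters.

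**Working it through.** **Inputs from the article.** Items p = 30; five patients per item; separate data for the two factor analyses. The plan's own figures reproduce: 5 × 30 = 150, and 2 × 150 = 300. The upper end of the rule would give 7 × 30 = 210, and 420 in total.

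**Inputs assumed.** The article does not state the number of factors, the loadings or the factor correlations. The check used 1 to 6 factors in the formula and 1, 3 or 5 in the 30-item simulations. Loadings were 0.5 to 0.8, with factor correlation 0.3 and simple structure. The 0.90 standard is also an assumption.

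**Formulas for a correct model with k factors.**

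- df = p(p+1)/2 − [2p + k(k−1)/2]
- Expected GFI ≈ p / (p + 2df/(N−1))
- AGFI = 1 − [p(p+1)/(2df)] × (1 − GFI)

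**At the planning figures, k = 3, N − 1 = 150.**

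- df = 465 − 63 = 402
- GFI ≈ 30 / (30 + 804/150) = 30 / 35.36 = 0.848
- AGFI ≈ 1 − (465/402) × 0.152 = 0.824

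Varying the factors from 1 to 6 moves expected GFI only between 0.847 and 0.851, and AGFI between 0.823 and 0.824.

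**Sample needed for an expected value of 0.90 at 30 items.** For GFI, N − 1 = 18df/p = 18 × 402/30 = 241, so N is about 243 (235 to 244 across 1 to 6 factors). For AGFI, N is about 285.

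**The ratio rule itself keeps GFI low.** With 3 factors and five patients per item, using N in place of N − 1: 20 items and N = 100 give 20/(20 + 334/100) = 0.857; 40 items and N = 200 give 40/(40 + 1474/200) = 0.844.

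**Simulation.** The true model was fitted by maximum likelihood, 300 data sets per setting. The table shows loadings of 0.7.

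| Items | Factors | N | Mean GFI | Mean AGFI | GFI ≥ 0.90 | AGFI ≥ 0.90 |
|---|---|---|---|---|---|---|
| 30 | 3 | 151 | 0.848 | 0.824 | 0% | 0% |
| 30 | 5 | 151 | 0.851 | 0.824 | 0% | 0% |
| 30 | 5 | 210 | 0.888 | 0.869 | 5% | 0% |
| 30 | 5 | 300 | 0.919 | 0.905 | 100% | 79% |
| 24 | 4 | 151 | 0.880 | 0.853 | 1% | 0% |
| 20 | 4 | 151 | 0.901 | 0.874 | 54% | 2% |
| 18 | 3 | 151 | 0.911 | 0.885 | 87% | 11% |
| 15 | 3 | 151 | 0.928 | 0.901 | 99.7% | 52% |
| 12 | 3 | 151 | 0.947 | 0.919 | 100% | 86% |

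Across all 30-item settings at N = 151, including one with five-category responses, the highest GFI was 0.873 and the highest AGFI 0.851. In the same data sets RMSEA was at or below 0.06 every time. CFI averaged 0.94 to 0.99 and reached 0.90 in 83% to 100%; the lowest shares came with loadings of 0.5.

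**A looser standard.** A separate simulation used 30 items, 3 factors, loadings 0.6 to 0.7, factor correlation 0.4 and N = 150. With 0.85 as the standard, GFI passed in 34% to 40% of data sets and AGFI in 0% to 1%.

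**The case against.** The strongest reply is that the article never states the rule that would do the harm. It gives no 0.90, and numerical thresholds are commonly left to an analysis plan. It does not say that missing one index counts as misfit. On an overall reading, CFI and RMSEA, both already listed, would usually carry a correct model through. The stated consequence is a review or a reconsideration, which does not oblige anyone to change an item. All of that stands. The absence of a cut-off is therefore not the point made here.

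Two stronger readings are tempting, and neither is supported.

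- A reader might infer that a correct model can never reach 0.90 under this plan. That holds in practice only with nearly all items kept and close to the minimum sample. The 30 items are a planning assumption, items may be dropped or merged before the confirmatory step, 150 is a floor, and no equal split is stated. At 20 items GFI reaches 0.90 about half the time. AGFI recovers more slowly: 2% at 20 items and about half at 15.
- A reader might infer that the plan re-tests a revised structure on data already used. The article describes no re-test of any kind. What can be said is narrower: it budgets two samples, both are used once the first confirmatory analysis is run, and its Results section moves from Phase 3 to publication of the scale.

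What the reply does not remove is that the item count, sample size, indices and consequence of misfit are all stated. At those figures, two of the four indices largely reflect sample and model size.

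**Conclusion.** The point holds in a conditional form. At the article's own planning figures, GFI of about 0.85 and AGFI of about 0.82 are what a correct model is expected to produce. If a conventional 0.90 standard were applied to either, a sound structure would be flagged and sent to item review or a reconsidered exploratory analysis. At 0.85 it would still fail on GFI in more than half of data sets and on AGFI almost always. The size of the problem depends on how many items survive to the confirmatory step, how far its sample exceeds 150, and whether GFI or AGFI alone can signal misfit.

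The formula and simulations assume simple structure and a true model. They show that low GFI and AGFI would be uninformative here; they say nothing about how well the actual scale will fit.

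**What to change.** In the Primary Investigation section, base the fit decision on CFI, RMSEA with its 90% CI, and SRMR. Report GFI and AGFI descriptively at most. SRMR was not part of the simulations above, so its standard should be checked at the planned sample size before it is fixed. CFI also needs a considered standard: with loadings of 0.5 a correct 30-item model reached 0.95 in only 39% to 48% of data sets.

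Add a sentence to this effect: if the structure is re-specified after the confirmatory analysis, it will be reported as exploratory, and structural validity will not be claimed as confirmed until the structure has been tested in new data.

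The cost is wording and standard software output, and by the article's timetable Phase 3 had not started. The downside is a less favourable claim if the first confirmatory analysis fails. Keeping AGFI as a deciding index would instead need about 285 patients in the confirmatory sample for an expected value of 0.90 at 30 items. With 150 for the exploratory analysis that is 150 + 285 = 435 in total, and many correct models would still fall short.
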